## Abstract

**Background:**

Community- and strengths-based psychosocial interventions are central to mental health and psychosocial support guidelines, but rigorous evidence regarding the effectiveness of these interventions is limited. The complexity and variability that is inherent to many community-based psychosocial interventions requires innovative strategies in order to facilitate the comparability and synthesis across research studies without compromising the fit and appropriateness of interventions to specific study populations and context. *Entre Nosotras* is a community-based psychosocial intervention developed for migrant and host community women that is designed to be flexible enough to enable integration of external intervention components and adaptable to diverse study contexts and populations. This protocol describes a study that aims to evaluate the appropriateness, acceptability, and feasibility of integrating a standardized stress management intervention into *Entre Nosotras*.

**Methods:**

This study will evaluate the appropriateness, acceptability, feasibility, and safety of intervention and research procedures for a cluster randomized comparative effectiveness trial conducted in Ecuador and Panamá with migrant and host community women. In this feasibility trial, we will allocate communities nested within the three study sites to the integrated *Entre Nosotras* + stress management intervention versus *Entre Nosotras* alone through stratified randomization. Migrant and host community women residing in these study communities who report low to moderate levels of distress will be allocated to the intervention condition that their community is assigned (*n* = 220 total). We will collect quantitative measures of psychosocial wellbeing, psychological distress, coping, social support, and functioning from study participants. We will collect quantitative measures of fidelity and facilitator competencies through observation and facilitator self-assessment. Data on appropriateness, acceptability, feasibility, and safety will be gathered from participants and facilitators through quantitative assessments at 0, 5, and 10 weeks post-enrollment and qualitative interviews conducted with all facilitators and a subset of 70 study participants during the post-intervention follow-up period.

**Discussion:**

Results from this feasibility trial will determine whether a multi-site cluster randomized comparative effectiveness trial of an adaptable community-based psychosocial intervention for migrant and host community women is relevant, acceptable, and feasible.

**Trial registration:**

ClinicalTrials.gov identifier: NCT05130944. Registered November 23, 2021—retrospectively registered.

## Background

By the end of 2020, over 80 million people were forcibly displaced due to persecution, conflict, violence, human rights violations, and other emergencies globally [1]. Displaced populations face increased exposure to potentially traumatic events and ongoing adversity that increase their risk of mental health and psychosocial problems [2–4]. The evidence supporting the effectiveness of mental health and psychosocial support (MHPSS) programs in humanitarian settings has grown over the past few decades [5, 6]. However, existing evidence is primarily available for focused psychological interventions to treat mental health problems adapted from interventions developed in high-income contexts as opposed to promotion and prevention programs designed within the target population that focus on mitigating risk of mental health problems and enhancing psychosocial wellbeing. Furthermore, few MHPSS interventions have focused on the social dimension of mental health and psychosocial wellbeing [5]. Social difficulties such as isolation, discrimination and xenophobia, and lack of community support and connectedness are often salient problems affecting migrant communities [7, 8]. These outcomes are rarely included as MHPSS intervention targets or outcomes in humanitarian settings.

Community- and strengths-based psychosocial interventions are central to MHPSS recommendations in humanitarian settings despite remaining underrepresented in existing research evidence [6, 9, 10], and are considered a critical research priority [11]. Available evidence from evaluations of psychosocial prevention and promotion interventions is heterogeneous with respect to the types of interventions and evaluation approaches, creating challenges for comparability and evidence synthesis [6, 12]. Researchers have argued that in order to advance the evidence on psychosocial interventions there needs to be better specification of interventions to enable replication, design and tailoring of psychosocial interventions for specific subgroups (e.g., women) and subgroup-specific outcomes, and rigorous evaluations of community-based interventions that enhance psychosocial wellbeing through improved social and community-related processes [5, 6, 13].

In the proposed multi-site study, we aim to examine the feasibility of a community-based psychosocial intervention for women using an adaptable, but manualized process to balance the need to ensure fit with the need for replicability in existing research on psychosocial interventions [14]. The intervention was designed to be adaptable by specifying the components of the intervention that are fixed and those that are adaptable. The adaptable components are modifiable activities that can be substituted with more culturally or contextually relevant activities that are expected to achieve the same objective as the original activity. This study proposes to use a comparative effectiveness design that enables the intervention components targeting social processes, which we hypothesize may require more tailoring to fit the socio-cultural context, to be adaptable across settings while testing the integration of a standardized stress management component on psychosocial wellbeing for women in three diverse contexts. A comparative effectiveness design utilizing an equal attention control also minimizes the risk of information bias that threatens the validity of many wait-list controlled trials of psychosocial interventions (e.g., due to placebo effects).

The proposed research aims to address major gaps in evidence on MHPSS interventions and incorporates processes to promote local adaptability and fit without compromising the intervention rigor. A community-based approach that combines testable, yet locally adaptable components to improve mental health, coping, functioning, social support and connectedness, and a sense of safety is needed to effectively promote the wellbeing of displaced women affected by chronic adversity and humanitarian emergencies.

### Objectives

The purpose of the current protocol is to describe a feasibility cluster randomized trial examining the integration of a scalable stress management intervention into *Entre Nosotras* (‘among/between us’), a community-based psychosocial intervention for migrant and host community women in Ecuador and Panamá. The two study conditions include (1) *Entre Nosotras*, a flexible and adaptable women’s group intervention designed to mobilize social support, strengthen community connectedness, and stimulate collective action to promote the safety and wellbeing of women (standard intervention); to (2) *Entre Nosotras* with an additional scalable stress management intervention (enhanced intervention). The objective of this feasibility trial is to examine the appropriateness, acceptability, feasibility, and safety of *Entre Nosotras* as well as the integrated stress management component and to collect data to inform the design of a definitive cluster randomized comparative effectiveness trial.

## Methods/design

### Study setting

Latin America has recently experienced increasing levels of forced migration due to political conflict, economic crises, climate-related events, community violence, and other factors. Panamá hosts refugees and migrants from the Northern Triangle (Guatemala, Honduras, El Salvador), Nicaragua, Colombia, and Venezuela, among other countries [15]. Ecuador has long been a host country for displaced persons from Colombia and, more recently, Venezuela [16]. Migrants in these contexts face mental health and psychosocial problems, protection risks, and disrupted social and community support systems [17]. Gaps in the provision of psychosocial services, despite the high prevalence of psychosocial problems and threats to the safety and wellbeing of refugees and migrants, persist in both countries and have been exacerbated due to the COVID-19 pandemic [18].

The proposed research will be conducted in three sites where the implementing partner, HIAS, an international non-governmental refugee protection organization [19], is currently providing services to migrants in Ecuador (Guayaquil and Tulcán) and Panamá (Panamá City area). Guayaquil is the largest city in Ecuador located in the coastal region and is a destination for many migrants from Colombia and Venezuela. Tulcán is located in the highlands of Ecuador on the border with Colombia and is primarily rural and often a temporary place of transit for migrants. Panamá City is the capital of Panamá and a destination for migrants, primarily from Central and South America. Many migrant communities live in peri-urban areas surrounding Panamá City. The majority of migrants in Panamá and approximately half of migrants in Ecuador are female, most of whom are of reproductive age [20]. These three sites were selected because they have large and increasing populations of forced migrants and are diverse in terms of urbanicity, service delivery systems, populations, and other implementation factors.

### Study design

We will conduct a feasibility cluster randomized trial and mixed-methods process evaluation in nine communities across the three study sites. The randomization procedure will be stratified by site. Within each of the three sites, we will randomly allocate at least half of the communities to receive the integrated intervention (*Entre Nosotras* with a standardized stress management component) as compared to *Entre Nosotras* alone. A definitive trial with this design will allow us to examine whether adding a structured stress management component to *Entre Nosotras* enhances study outcomes beyond any effects derived from the *Entre Nosotras* intervention alone. This design also allows for flexibility in the specific activities within the community-based women’s group (*Entre Nosotras*) component to be tailored to the local population and context in each of the three study sites and may serve as a model for future research balancing replicability and fit.

### Sequence generation

Communities (clusters) will be allocated to study condition using a random number generator in Stata by a researcher not affiliated with the project.

### Allocation concealment mechanism

Since this is a cluster-randomized design there will be no allocation concealment mechanism.

### Blinding

Only feasibility trial participants will be blinded to the conditions of the two arms.

### Intervention

*Entre Nosotras* is a community- and strengths-based intervention designed to mobilize social support, strengthen community connectedness, and stimulate collective action to promote the safety and wellbeing of women. The intervention was selected and designed through a formative qualitative research and community consultation process, which is described in detail within a forthcoming publication. Through this formative research process, we identified social problems (e.g., interpersonal violence, xenophobia and discrimination, social isolation, and loneliness) and psychological problems (e.g., emotional distress, sadness) to be among the most salient problems affecting migrant women in these communities. Through a community consultation and design process, women recommended a dynamic and interactive group intervention that mobilized social support and leveraged community resources, while also providing skills to help cope with psychological distress and improve safety. With this information, we designed *Entre Nosotras* to target the social problems and processes that we discovered during this formative research and further identified a standardized, stress management intervention for coping with psychological distress that could be integrated to enhance the *Entre Nosotras* components.

The intervention includes five weekly sessions lasting approximately 2 to 3 h each delivered by female facilitator pairs within the community. The intervention is based on the HIAS Mental Health and Psychosocial Support Curriculum [21], principles of Psychological First Aid [22–24], and the Community Action Cycle [25], which is intended to generate community-led problem solving around priority issues affecting participants’ wellbeing. The sessions include a series of fixed and modifiable components. The fixed components of the intervention are the scaffolding of the intervention that introduce the topics for each session and guide the facilitator through the session (see Table 1). These fixed components include specific objectives, brief facilitator scripts, and tips for the facilitator, including possible adaptations for remote delivery. The modifiable components make up the majority of the intervention and include suggested activities that align with the session objectives. The program implementers/managers are encouraged to substitute these suggested activities for ones that are culturally relevant and expected to achieve the specified objectives. This adaptable manual is designed to maintain consistency around the objectives and concepts that are covered within the sessions (i.e., function), while allowing for variability in how these concepts are expressed and engaged with in groups (i.e., form).

**Table 1 Tab1:** Overview of the intervention

Session	Objectives
1. Building trust, security, and connection	• Build trust and group identity • Collectively set group expectations, rules, and goals • Introduce concepts of coping and grounding (in enhanced condition only)
2. Psychosocial wellbeing	• Define the concept of psychosocial wellbeing and its dimensions • Describe the factors that contribute to psychosocial wellbeing, including the impacts of adversity • Practice grounding as a coping skill (in enhanced condition only)
3. Gender, gender-based violence, and safety	• Reflect on concepts related to gender, wellbeing, and protection • Identify resources to promote the safety and wellbeing of women • Introduce unhooking from difficult thoughts and feelings as well as acting according to your values as coping skills (in enhanced condition only)
4. Strengths and psychosocial resources	• Identify social and psychological strategies and resources to support safety and psychosocial wellbeing • Mobilize peer support • Revisit acting on your values and introduce being kind as coping skills (in enhanced condition only)
5. Community resources	• Identify community resources that promote protection, safety, and wellbeing • Strengthen community support networks • Introduce making room as a coping skill (in enhanced condition only) • Generate a group support and action plan for the future

For example, in Latin America there is a long history of using theater to generate collective discussion and action around social issues [26]. In session 4, *Entre Nosotras* uses this ‘theater of the oppressed’ methodology to generate strategies to support women who are affected by family problems/violence, community tension, and xenophobia. However, in other contexts, there may be more culturally appropriate approaches to generate discussion and collective action on sensitive social issues, which can be used to substitute the theater of the oppressed activity. Additionally, within this study there were notable differences in the intervention across the study sites. For example, in Ecuador, the intervention concludes with a *pamba mesa*, which is a traditional communal meal that symbolizes social solidarity. In Panamá, the final session closes with the participants sharing a small gift (e.g., crafts, bracelets) made for another member of the group along with a discussion of what they gained from the intervention and how they plan to sustain the group. They are also invited to bring something to share with the group that, similarly to *pamba mesa*, may include food. Each of these activities shares the same function (e.g., reinforcing social connectedness and sustained group identity), but applies a form that fits the local context and traditions.

The *stress management* component that we have integrated into the *Entre Nosotras* intervention for the experimental condition is based on the World Health Organization’s Doing What Matters in Times of Stress intervention [27], a self-guided stress management intervention that is intended to provide practical skills to help people cope with psychological distress. It includes an illustrated guide along with optional audio exercises that are based on Acceptance and Commitment Therapy (ACT), a type of cognitive behavioral therapy that incorporates mindfulness approaches to develop skills for managing difficult thoughts and feelings [27, 28]. Doing What Matters in Times of Stress includes five skills-based tools: (1) grounding; (2) unhooking from difficult thoughts; (3) acting on your values; (4) being kind; and (5) making room [27]. As shown in Table 1, we distributed activities to support the development of these skills across the five sessions. Within the sessions, the facilitators provide an overview of the skill(s) and the participants practice the skill at least once during the session with the support of audio exercises developed and made publicly available by the World Health Organization in thirteen languages (https://cdn.who.int/media/docs/default-source/mental-health/doing-what-matters-audio-audio-links-in-different-languages.pdf?sfvrsn=1f449f8d_16). Each session ends with homework that involves setting a goal for practicing the skill, which is revisited during the check-in at the beginning of the following session.

### Participants and procedures

#### Study eligibility

The target population for this study includes Spanish-speaking adults who identify as women, reside in the study community, and are willing and able to engage in the intervention. We aimed to recruit a mix of both migrant and host community women. We plan to recruit 70–80 women from each of the 3 sites (*n* = 220 women total; *n* = 20–40 women per community) into the feasibility trial. The eligibility criteria are as follows:

#### Inclusion criteria

We will include adult (18+ years) women residing in the study community who speak and understand Spanish.

#### Exclusion criteria

We will exclude participants if they report severe psychological distress (Kessler-6 score > 13), disclose suicidal thoughts or feelings, or display signs of cognitive impairment that would prevent participation in a group psychosocial intervention during the screening interview. Participants who are excluded for these reasons will be referred to appropriate services within HIAS or through partner implementing organizations.

A subset of participants from the feasibility trial (*n* = 10 per community, or until we reach saturation) as well as all intervention facilitators will be selected to complete qualitative semi-structured interviews after the intervention period. Participants will be purposively selected using maximum variation sampling to represent a range in level of engagement, level of distress, among other factors that emerge as important contributors to implementation success.

### Recruitment, screening, and assessment procedures

All participants will be recruited through referral from HIAS staff, community outreach workers, and community leaders. Interested individuals will be connected by phone or in person with members of the research team, who will provide further information about the study. After providing further information, research assistants will invite interested individuals to complete a brief screening assessment. Verbal consent must be provided prior to commencing the screening. We will obtain written informed consent from eligible participants prior to administering a baseline assessment. Within 2 weeks of the baseline assessment, participants will attend the first session of the *Entre Nosotras* group to which their community was randomly allocated (enhanced vs. standard condition). Follow-up assessments will be conducted by a research assistant within 1-week post-intervention and 5 weeks post-intervention. Facilitators and participants selected to participate in the process evaluation will be invited to participate in a qualitative interview occurring within the post-intervention follow-up period (i.e., between end of intervention and 5 weeks post-intervention).

Assessments are designed to be conducted remotely or in person, depending on COVID-19 policies and recommendations. Participants who complete the assessments in person will be provided with reimbursement for their transportation costs and a take-away snack as an incentive for their participation. Participants who complete the assessments remotely will be provided with airtime or connectivity reimbursement for their participation.

### Outcomes

This feasibility trial aims to assess the appropriateness, acceptability, feasibility, and safety of implementing and evaluating *Entre Nosotras*, including when integrated with a stress management component, for migrant and host community women in Ecuador and Panamá. These outcomes will determine whether the study should progress to a definitive cluster-randomized comparative effectiveness trial and whether any research design or intervention adaptations are needed. These feasibility trial outcomes will be assessed using indicators and means of verification that are measured at the participant, service, and implementation level [29]. Table 2 details the outcomes, indicators that will determine progression to the definitive trial, means of verification, and assessment time points.

**Table 2 Tab2:** Study outcomes, indicators, and means of verification

Outcome	Indicator(s) for progression to definitive trial	Means of verification	Participants assessed	Time points			
				Screening/baseline	Intervention ***(5 weeks)***	Post-intervention	5-week follow-up
Appropriateness	**Eligibility:** > 50% of persons are screened are eligible	Routine study monitoring forms	Screened individuals	X			
	**Sensitivity to change:** Small to moderate within-group changes in outcome measures (*d* > 0.2)	Brief-COPE, K-6, OSS, PWI, WHODAS	Participants	X		X	X
	**Intervention fidelity:** > 75% fidelity to the intervention elements	Fidelity assessment^a^	Facilitator pairs		X		
	**Stakeholder perspectives:** Participants and facilitators report that the intervention and research procedures are appropriate and relevant to the needs of host and migrant women	Qualitative interviews	Participants, facilitators			X	X
Acceptability	**Intervention engagement and completion:** > 85% of participants attend first session; > 67% participants complete at least 4 sessions	Routine study monitoring forms	Participants		X		
	**Intervention usability:** Facilitators consider the intervention to have above average usability (IUS Score > 68).	Intervention Usability Scale	Facilitators		X		
	**Stakeholder perspectives:** Participants and facilitators report that the intervention and research procedures are acceptable and safe for host and migrant women	Qualitative interviews	Participants, facilitators			X	X
Feasibility	**Recruitment rate:** Average rate of enrollment is 5 women per week, at minimum, in each community	Routine study monitoring forms	Participants	X			
	**Randomization:** No moderate to large differences (*d* > 0.5; Φ > 0.3) in baseline characteristics between study conditions within study sites	Demographics, Brief-COPE, K-6, OSS, PWI, WHODAS	Participants	X			
	**Attrition:** > 80% of participants complete baseline, post-intervention, and follow-up assessments	Demographics, Brief-COPE, K-6, OSS, PWI, WHODAS	Participants	X		X	X
	**Fidelity to research procedures:** No major protocol deviations	Routine study monitoring forms	Research assistants	X	X	X	X
	**Facilitator competencies:** An average score of > 2 on competency items, suggesting partially-fully demonstrating the competencies during intervention implementation	ENACT^a^	Facilitators		X		
	**Contamination:** Stress management components from the experimental conditions are included in all sessions for groups randomized to the enhanced intervention and none of the sessions for groups randomized to the standard intervention	Fidelity assessment^a^	Facilitator pairs		X		
	**Performance of outcome measures:** All outcome measures display adequate construct validity and internal consistency	Brief-COPE, K-6, OSS, PWI, WHODAS	Participants	X		X	X
	**Stakeholder perspectives:** Participants and facilitators report that the intervention and research procedures are feasible, adoptable, scalable, and sustainable. Participants and facilitators identify barriers and facilitators to implementation as well as strategies for overcoming/leveraging these factors.	Qualitative interviews	Participants, facilitators			X	X
Safety	**Adverse events:** Detected in < 10% of participants; no serious adverse events attributed to study participation	Adverse event reporting	Participants	X	X	X	X
	**Stakeholder perspectives:** Participants and facilitators report that the intervention and research procedures are acceptable and safe for host and migrant women	Qualitative interviews	Participants, facilitators			X	X

*Abbreviations*: *IUS* Intervention Usability Scale, *K-6* Kessler-6, *OSS* Oslo Social Support Scale, *PWI* Personal Wellbeing Index, *WHODAS* World Health Organization Disability Assessment Schedule

^a^Fidelity assessment includes a self-administered assessment completed by the facilitator pair at the end of each session as well as an external assessment completed by a member of the research team at two or more sessions per group. Six items from the ENACT that were relevant for a non-clinical, group psychosocial intervention (non-verbal communication and active listening; verbal communication; rapport building and self-disclosure; exploration, interpretation and normalization of feelings; demonstration of empathy, warmth, and genuineness; elicitation of feedback when providing advice, suggestions, and recommendations) were selected to assess facilitator competencies during the facilitator training and are also evaluated by a member of the research team at the 2+ sessions during which they administer the external fidelity assessment

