
### Sample size

At least two groups (range 2–4) will be implemented per study community. We aim to enroll up to 220 women (10 women per group). A summary of the target sample size (participants, groups) by study site and community is provided in Table 3. This sample size is comparable to prior feasibility trials of group psychosocial interventions and will enable us to sufficiently pilot the study procedures and evaluate the relevance, acceptability, and feasibility of the intervention and trial design [53, 54]. A sample size of 220, is expected to provide sufficient power to evaluate the construct validity and internal consistency of the study outcome measures in a confirmatory factor analysis under most scenarios (e.g., number of parameters and magnitude of loadings) [55].

**Table 3 Tab3:** Sample size by site and community

Site	Communities (***unit of randomization)***	Number of groups	Number of participants
Guayaquil, Ecuador	• La Florida • Mapasingue and Martha de Roldós	7	70
Tulcán, Ecuador	• Julio Andrade • San Pedro de Huaca • Santa Martha de Cuba and San Luis	7	70
Panamá City, Panamá	• Arraijan • La Chorrera • Panamá City • San Miguelito	8	80

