### Planned analyses

#### Quantitative data analysis

##### Descriptive analyses of baseline data

We will use descriptive statistics to characterize quantitative indicators of relevance, acceptability, and most indicators of feasibility. Descriptive statistics will include mean with standard deviation and/or median with interquartile range for continuous variables. Categorical variables will be displayed using frequencies and proportions. We will explore the distribution of demographic and psychosocial characteristics across the study communities and intervention conditions to characterize heterogeneity across sites and identify any major baseline imbalances between study conditions. We will calculate effect sizes to explore the magnitude of baseline differences between study conditions (Cohen’s *d* for continuous variables, Φ for categorical variables) and estimate the significance of this difference using mixed effects models accounting for clustering within communities and sites.

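### The Table 2 randomization indicator (no within-site d > 0.5 or Φ > 0.3) allows nothing for chance, few communities or multiple comparisons, so correct randomization will often breach it

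*Protocol article*

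**What the plan says.** The Outcomes section of the protocol describes Table 2 as listing the "indicators that will determine progression to the definitive trial". Under Feasibility, the randomization row permits no difference of d > 0.5 or Φ > 0.3 "in baseline characteristics between study conditions within study sites", verified by "Demographics, Brief-COPE, K-6, OSS, PWI, WHODAS". The wording is absolute. It names no permitted number of breaches and makes no adjustment for clustering.

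Under Study design, "The randomization procedure will be stratified by site", and within each site "we will randomly allocate at least half of the communities to receive the integrated intervention". Table 3 (Sample size) gives the units of randomization:

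- Guayaquil has two ("La Florida • Mapasingue and Martha de Roldós"), with 70 women.
- Tulcán has three, with 70 women.
- Panamá City has four, with 80 women.

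The section on descriptive analyses of baseline data plans Cohen's d and Φ between conditions. It will also "estimate the significance of this difference using mixed effects models accounting for clustering within communities and sites". The clustering is therefore recognised in the models but not in the progression threshold.

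**The concern.** A progression indicator should be likely to pass when the procedure it judges has been carried out properly. This one has two separate weaknesses.

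- **Few clusters.** With one or two communities per arm in a site, ordinary differences between places pass straight into the arm difference.
- **Multiplicity with zero tolerance.** Five scales in three sites give 15 comparisons before any demographic variable is counted, and a single breach fails the indicator. This operates even if there is no clustering at all.

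Guayaquil raises a further point. With one community per arm, exchanging the two allocations changes the sign of the difference but not its size. Absolute d and Φ are then properties of the two communities, and cannot show whether randomization worked.

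What is at stake is the decision after the pilot. A sound procedure may be marked as failed and redesigned without need, or the indicator may be set aside after the event, which defeats the purpose of fixing it in advance.

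**Working it through.** **Inputs from the protocol.** Table 3: 7 + 7 + 8 = 22 groups of 10 women, and 22 × 10 = 220, which reproduces the stated total. Thresholds 0.5 and 0.3 come from Table 2. The protocol states no false-alarm rate for this indicator, so there is none to reproduce.

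**Assumptions.** Community sizes (enhanced | standard) are 40 | 30 in Guayaquil, 20+20 | 30 in Tulcán and 20+20 | 20+20 in Panamá. These fit Table 3, the 2–4 groups per community and the rule of at least half enhanced. The community ICC is not given and is varied over 0, 0.01, 0.02 and 0.05. The number of demographic variables is not given; the five scale totals alone are the floor.

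**One characteristic, one site.** With no true difference,

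Var(d) = sum over the two arms of [ICC × Σm² / (Σm)² + (1 − ICC) / n],

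where m are the community sizes and n the arm size, and P(|d| > 0.5) = 2 × [1 − Φ_N(0.5 / SE)], with Φ_N the standard normal distribution function. At ICC 0.05:

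- Guayaquil: 0.05 × 2 + 0.95 × (1/40 + 1/30) = 0.1554, SE 0.394, P = 20.5%.
- Tulcán: 0.05 × 1.5 + 0.95 × (1/40 + 1/30) = 0.1304, SE 0.361, P = 16.6%.
- Panamá: 0.05 × 1 + 0.95 × (1/40 + 1/40) = 0.0975, SE 0.312, P = 10.9%.

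At ICC 0 the three chances are 3.8%, 3.8% and 2.5%.

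**One characteristic, any site.** At ICC 0.05, 1 − 0.795 × 0.834 × 0.891 = 41%. At ICC 0 it is 9.9%.

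**Five scales, any site.** If the scales were independent, 1 − (1 − 0.409)^5 = 93% at ICC 0.05, and 1 − (1 − 0.099)^5 = 41% at ICC 0. Simulation with sample standard deviations and between-scale correlations from 0 to 0.5 gives the ranges below. The last column adds demographics as 6 continuous and 4 binary characteristics (correlation 0.3 to 0.5 among the continuous ones), with the binary ones judged on Φ.

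| Community ICC | Five scales only | 6 continuous + 4 binary |
|---|---|---|
| 0 | 37–44% | 47–53% |
| 0.01 | 53–64% | 67–75% |
| 0.02 | 68–76% | 81–85% |
| 0.05 | 89–95% | 96–98% |

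Binary characteristics must be judged on Φ because it is the harder threshold to breach: in Guayaquil at ICC 0.05 the chance is 12.4% for Φ > 0.3, against 20.5% for d > 0.5.

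**The same threshold on a pooled difference.** Weight the site differences by 70/220, 70/220 and 80/220. At ICC 0.05, Var = (70/220)² × (0.1554 + 0.1304) + (80/220)² × 0.0975 = 0.0418, SE 0.204, P = 1.4% per characteristic, and 1 − (1 − 0.0145)^5 = 7% over five scales. Simulation gives about 0.1–0.2% at ICC 0, 1–2% at 0.02 and 6–9% at 0.05.

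**The case against.** The case on the other side is substantial, and several parts of it stand.

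**A breach is not a stop.** A reader might infer a hard go/no-go rule. The documents do not support that: the Outcomes section also uses the indicators to decide whether adaptations are needed, and the Discussion says that problems will lead to modified procedures.

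**Within-site balance is the stated question.** The feasibility measures section asks whether randomization produced balanced groups within site. Large imbalance from few communities is useful knowledge for the definitive design. It would be wrong to say that the differences carry no information; the fault lies in using them as pass/fail.

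**Baseline comparison has a purpose here.** One might argue that the baseline models test a null hypothesis which randomization already makes true. That is not safe in this trial. The protocol has no allocation concealment, blinds only participants, and recruits by referral from staff, outreach workers and community leaders. Recruitment could differ by arm after communities are allocated, and baseline data may reveal it.

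**No significance test within Guayaquil is planned.** A reader might object that such a test cannot be estimated with one community per arm. The planned models span communities and sites, and no p-value enters the Table 2 indicator.

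**Pooling loses something.** A difference of d = 1.5 in one 70-woman site and none elsewhere gives 1.5 × 70/220 = 0.48 and passes; opposite differences can cancel. The remedy therefore has to keep the within-site results in view.

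None of this answers the central point: the threshold as written has no allowance for chance, clustering or multiplicity.

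**Conclusion.** The concern holds in a conditional form. Under correct randomization the indicator is breached in about 37–44% of trials on the five scales if there is no community clustering. It is breached in more than half once the community ICC is about 0.01 or higher. A reader might conclude that it will usually fail whatever the circumstances; that is not supported, because at ICC 0 the five-scale figure is below one half, and the protocol states neither the ICC nor the number of demographic variables. Nor are the small numbers of communities the only cause, since the breach rate at ICC 0 comes from multiplicity alone.

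The assumed split of communities matters less: 50 v 20 in Tulcán instead of 40 v 30 raises the single-characteristic chance at ICC 0 from 3.8% to 5.9%. The Guayaquil point needs no assumption beyond one community per arm.

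This should be fixed before the progression decision. It touches one indicator among many in a feasibility trial, and affects no effectiveness inference and no participant's safety.

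**What to change.** In the randomization row of Table 2:

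1. Stop using within-site breaches as a pass/fail progression indicator.
2. Apply the 0.5 and 0.3 thresholds to one site-stratified pooled standardized difference per characteristic, using all 220 women.
3. Continue to report every within-site difference against the same thresholds, as a review flag. A flag would inform covariate adjustment or constrained randomization in the definitive trial, and prompt a check for differential recruitment.
4. List the demographic characteristics the indicator covers, so that the number of comparisons is fixed.

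The baseline mixed models may stay as description, with a sentence saying that they do not feed the progression decision.

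The cost is wording only, with no new data. There is a small downside: an imbalance confined to one site, or opposite imbalances that cancel across sites, leads to review rather than formal failure. The pooled rule is also not immune to strong clustering, as its 6–9% five-scale breach rate at ICC 0.05 shows.
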